**STATISTICAL ANALYSIS PLAN (5 October 2020)**

The study is powered for the primary endpoint making the hypothesis that 60% of patients with lower respiratory tract infection due to COVID-19 and suPAR≥6 ng/ml upon hospital admission will develop SRF. To decrease this to 45% with power of 90% at a 5% level of significance, two hundred sixty (260) patients need to be enrolled. Taking into consideration, the single-arm study design, 500 patients should be enrolled to make results more robust. Data will be analyzed for the intention-to-treat (ITT) population.

An interim analysis will be conducted after completion of the 30-day follow up of the first 130 patients, i.e. 50% of the number of patients needed to be enrolled as calculated by power analysis. Parallel comparators receiving standard-of-care treatment (SOC) will be used all patients hospitalized at the same time period in eight departments of Internal Medicine in tertiary hospitals of Athens who were participating in the registry of the Hellenic Sepsis Study Group without participating in the SAVE trial ([www.sepsis.gr](http://www.sepsis.gr)). Data and biosample collection is done in the SOC comparators after written informed consent. The same inclusion and exclusion criteria will apply in the parallel comparators under SOC as in patients participating in the SAVE trial. Data collection in these departments has been approved by the Ethics Committees of the participating hospitals. Propensity matching will be performed among comparators to the 130 patients enrolled in the SAVE trial, so as the 130 comparators will be fully comparable to all below criteria:

- Age
- Comorbidities, as expressed by the Charlson’s Comorbidity Index
- Admission severity scores namely pneumonia severity index (PSI), acute physiology and chronic health evaluation (APACHE) II score, SOFA score and WHO severity classification of COVID-19
- Co-administered treatment of azithromycin, hydroxychloroquine and dexamethasone

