Primary outcome and binary secondary outcomes as well as serious adverse event and adverse event rates between the two groups will be expressed as percentages and will be compared by the Fisher exact test, calculating also the respective odds ratios. The time to an event will be compared between the two groups by survival analysis. Stepwise Cox regression analysis will be conducted for the primary outcome and 30-day mortality. Quantitative secondary outcomes will be expressed as median values with respective interquartile range and will be compared by the Mann-Whitney U test.

The cost of hospitalization will be measured by adding the itemized cost of stay, drugs, and interventions and will be expressed as median with respective interquartile range. Salaries of nurse and medical stuff will not be included. Cost comparison will be done by the Mann-Whitney U test.

Qualitative baseline characteristics will be expressed as frequencies and percentages and compared by the Fisher exact test. Quantitative baseline characteristics will be expressed as mean values with standard deviation if following a normal distribution or median values with quartiles if following linear distribution. Comparisons of quantitative baseline characteristics will be done by the Student’s t-test or by the Mann-Whitney U test respectively. Paired comparisons will be done by the Wilcoxon’s rank-signed test. Non-parametric correlations will be done according to Spearman.

Analysis will be conducted with SPSS Version 25.0. All P values will be two-sided. Any P value <0.05 will be considered as statistically significant.

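### The only regression-adjusted analysis of SRF and 30-day mortality is a stepwise Cox model that is not said to keep the treatment term or the confounders

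*Supplement*

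**What the plan says.** The SAP of 5 October 2020 says of regression only that "Stepwise Cox regression analysis will be conducted for the primary outcome and 30-day mortality". It does not name the candidate variables, the direction of selection or the entry and removal limits. It does not say which terms are always retained, which set of patients is analysed, or whether matched pairs are taken into account.

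The same paragraph plans two other between-group analyses of these outcomes. Binary outcomes "will be compared by the Fisher exact test, calculating also the respective odds ratios", and "The time to an event will be compared between the two groups by survival analysis". Neither names a covariate. The general rules are "All P values will be two-sided" and "Any P value <0.05 will be considered as statistically significant".

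The comparators are not randomised. They are patients hospitalised over the same period "who were participating in the registry of the Hellenic Sepsis Study Group without participating in the SAVE trial". Confounding is also handled by design: "Propensity matching will be performed among comparators to the 130 patients enrolled in the SAVE trial". The SAP's matching variables are age, Charlson index, PSI, APACHE II, SOFA, WHO class, and treatment with azithromycin, hydroxychloroquine and dexamethasone. Matching is described for 130 against 130 patients at the interim analysis. None is described for the planned 500 patients.

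Protocol version 3.0 (Interim and Statistical Analysis) plans a percentage with 95% CI and the Fisher test, and no Cox model.

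**The concern.** With non-randomised groups, the purpose of a regression model is to estimate the treatment effect after allowing for differences at entry. Stepwise selection serves a different purpose: it keeps variables that are individually significant for the outcome. Two consequences follow.

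- A confounder that differs between groups but is weak on its own can be discarded, although several such variables together may matter.
- If treatment group is itself a candidate, its hazard ratio appears only in datasets where it passes the threshold. The estimates that appear are then too extreme on average, and their intervals take no account of the selection.

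At stake is the adjusted hazard ratio for SRF and for 30-day mortality. It matters most beyond the 130+130 set, where no matching is described and this model would be the only adjustment.

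**Working it through.** **1. Planning rates and the plan's own figure.** The documents give two pairs. The SAP assumes that "60% of patients with lower respiratory tract infection due to COVID-19 and suPAR≥6 ng/ml upon hospital admission will develop SRF", falling to 45%. The protocol (Number of Patients) assumes 55% falling to 35%. Both state 90% power at 5% and 260 patients. With two equal arms and a two-sided test,

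n per arm = [1.960·√(2p̄(1−p̄)) + 1.282·√(p₁(1−p₁)+p₂(1−p₂))]² / (p₁−p₂)².

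- 55% v 35%: (1.379 + 0.883)² / 0.04 = 128 per arm, 256 in total, which agrees with 260.
- 60% v 45%: (1.384 + 0.895)² / 0.0225 = 231 per arm, 462 in total, which does not.

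This mismatch is a separate matter and the present point does not rest on it. Both pairs are used below.

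**2. Implied hazard ratios.** Under proportional hazards, HR = ln(1−p₂)/ln(1−p₁).

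- SAP: ln 0.55 / ln 0.40 = 0.652
- Protocol: ln 0.65 / ln 0.45 = 0.539

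Expected events in 130+130 are 130 × (0.60+0.45) = 136.5 and 130 × (0.55+0.35) = 117.

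**3. Analytic check.** If treatment is kept roughly when its two-sided P value is below 0.05, the chance of losing it is about 1 − power. Schoenfeld's formula, power = Φ(√(d/4)·|ln HR| − 1.960), gives 0.704 with 136.5 events and 0.916 with 117. Losses of about 30% and 8% are therefore expected before allowing for covariates.

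**4. Simulation.** The documents supply the two rate pairs, 130 per group and follow-up to day 14. The rest is assumed: exponential event times; eight prognostic covariates with correlation 0.3 and log HR 0.15 to 0.20 per SD; entry at P<0.05 and removal at P>0.10; residual imbalance of 0, or of 0.2 SD per covariate in favour of the treated group. There were 250 runs per setting. Mean HR is the exponential of the mean log HR.

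| Setting | True HR | Fixed model: HR, coverage | Stepwise: treatment dropped | HR when kept, coverage | Stepwise, treatment forced in: HR, coverage |
|---|---|---|---|---|---|
| 60%→45%, balanced | 0.652 | 0.657, 95.6% | 36.4% | 0.600, 96.2% | 0.663, 94.0% |
| 60%→45%, imbalance | 0.652 | 0.629, 94.4% | 24.4% | 0.580, 93.7% | 0.620, 93.6% |
| 55%→35%, balanced | 0.539 | 0.548, 94.0% | 14.8% | 0.527, 96.2% | 0.553, 92.4% |
| No effect, balanced | 1.000 | 0.998, 94.4% | 94.4% | 1.009, 0% | 0.998, 94.0% |
| No effect, imbalance | 1.000 | 1.011, 97.2% | 97.2% | 0.887, 0% | 0.993, 96.4% |

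On average 3.1 to 3.7 of the eight true prognostic variables were discarded. Monte Carlo standard errors are √(0.364×0.636/250) = 3.0 points for the 36.4%, √(0.148×0.852/250) = 2.2 points for the 14.8%, and about 1.4 points for coverage near 95%.

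**5. Reading the table.** The harm comes mainly from leaving the treatment term open to selection. Once it is forced in, discarding covariates changed the mean HR little at these imbalances (0.620 against 0.629 for the fixed model).

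**The case against.** The strongest reply is that the SAP does not rely on this model. Four parts of that reply stand.

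- A reader might infer that the Cox model is the only adjusted analysis. It is not: matching adjusts the Fisher and survival comparisons in the 130+130 set.
- A reader might infer that a treatment effect is reported only when significant. The Fisher test, odds ratio and survival comparison cover the same outcomes whatever the stepwise result. Only the Cox HR could go missing. The documents give that HR no decision role: the primary endpoint is a rate, and the comparison with standard of care is listed as secondary.
- A reader might infer that the SAP allows treatment to be removed. It does not say either way. The same silence applies to matched pairs.
- A reader might infer that the intervals are generally invalid or that false positives rise. The simulation does not show this. Under a real effect, coverage when treatment was kept was 94% to 96%. Under no effect, stepwise and fixed models rejected equally often (5.6% each when balanced, 2.8% each with imbalance). The 0% coverage in the null rows follows from reporting only significant terms.

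The choice of method is not answered by this reply. No clause protects the treatment term or the matching variables, and no matching is described beyond the interim set.

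**Conclusion.** The point holds as one of model choice and missing specification. A selection procedure driven by outcome P values is a poor way to adjust a non-randomised comparison, and the SAP omits the clause that would make its treatment estimate dependable.

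The size depends on that clause. If treatment is open to selection, it is lost in about 36% of runs at 60% to 45%, and the mean HR when kept is about 0.60 against a true 0.652. At 55% to 35% it is lost in about 15%, and the exaggeration is slight (0.527 against 0.539). If treatment is forced in, bias is small, with coverage of 92% to 96%. These figures rest on assumed covariate effects, thresholds and imbalance, so they show the order of the problem and do not predict this trial's result. The documents do not support the stronger conclusion that the group comparison as a whole is unadjusted or biased.

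**What to change.** Replace the stepwise sentence in the SAP with a pre-specified Cox model for SRF and for 30-day mortality that states the following.

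- Treatment group and the SAP's matching variables are forced in: age, Charlson index, severity scores named in advance from PSI, APACHE II, SOFA and WHO class, and azithromycin, hydroxychloroquine and dexamethasone.
- Baseline suPAR is an added covariate. It is not one of the matching variables.
- No variable selection is used.
- Standard errors are clustered on pair where the set is matched.
- The HR with 95% CI is reported whatever its P value.
- A shorter covariate list for 30-day mortality is fixed now and not chosen after deaths are counted. The documents give no expected mortality from which to size it.
- The analysis set is named: the 130+130 matched set, the full enrolment, or both.

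For SRF the events suffice. With each variable as one term, the model has 8 to 11 terms (treatment, age, Charlson, one to four severity scores, three drugs, suPAR). The 117 to 137 events expected in 130+130 give at least 117/11 ≈ 10.6 per term. The cost is a small SAP edit and a slightly wider interval from keeping every covariate. For the matching variables and suPAR, it needs nothing beyond what matching and eligibility already require.

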## Patients’ visits and interventions (Appendix II)

*Day 1*

This visit will take place on the morning of the day of the start of treatment with the study drug. The following procedures will be done on that day:

- Recording of co-morbidities, co-administered drugs, past-history, SOFA score (Appendix III), absolute blood cell count and differential (if available) and biochemistry (if available)
- Scoring of the respiratory symptoms (Appendix IV).
- Administration of the study drug
- Recording of adverse events (AE) and severe adverse events (SAE)

*Day 2*

This visit will take place on the morning of the second day from the start of treatment with the study drug. The following procedures will be done on that day:

- Recording of co-administered drugs, absolute blood cell count and differential (if available) and biochemistry (if available)
- Recording of the presence or not of SRF (Appendix V)
- Recording of adverse events (AE) and severe adverse events (SAE)
- Administration of the study drug
- The visit may take place by phone call or through the internet in case of hospital discharge

*Day 3*

This visit will take place on the morning of the third day from the start of treatment with the study drug. The following procedures will be done on that day:

- Recording of co-administered drugs, absolute blood cell count and differential (if available) and biochemistry (if available)
- Recording of the presence or not of SRF (Appendix V)
- Recording of adverse events (AE) and severe adverse events (SAE)
- Administration of the study drug
- The visit may take place by phone call or through the internet in case of hospital discharge

*Day 4*

This visit will take place on the morning of the fourth day from the start of treatment with the study drug. The following procedures will be done on that day:

- Recording of co-administered drugs, absolute blood cell count and differential (if available) and biochemistry (if available)
- Recording of the presence or not of SRF (Appendix V)
- Recording of adverse events (AE) and severe adverse events (SAE)
- Administration of the study drug
- The visit may take place by phone call or through the internet in case of hospital discharge

*Day 5*

This visit will take place on the morning of the fifth day from the start of treatment with the study drug. The following procedures will be done on that day:

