## Secondary study endpoints

- Comparison of the primary endpoint with comparators receiving standard-of-care treatment
- Change of scoring for respiratory symptoms between days 1 and 7
- Change of scoring for respiratory symptoms between days 1 and 14
- Change of SOFA score between days 1 and 7
- Change of SOFA score between days 1 and 14
- Change of Peripheral Blood Mononuclear Cells’ (PBMCs) functionality between days 1 and 7
- Change of gene expression between days 1 and 7 (transcriptional, proteomic and metabolomic analysis)
- Change of plasma inflammatory mediators between days 1 and 7
- 30-day mortality
- 90-day mortality

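### Symptom-score and SOFA changes are compared without adjusting for the day-1 score, which costs power and leaves the unmatched symptom score open to regression-to-the-mean bias

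*Supplement*

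**What the plan says.** Protocol version 3.0, Secondary study endpoints, defines the four outcomes as changes. The symptom score is listed as "Change of scoring for respiratory symptoms between days 1 and 7", with a second entry that runs to day 14. SOFA has the same pair of entries, the later of them being "Change of SOFA score between days 1 and 14". The day-1 visit of trial patients includes both the SOFA score and "Scoring of the respiratory symptoms (Appendix IV"), and Appendix II confirms this.

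The SAP gives one between-group rule for such outcomes: "Quantitative secondary outcomes will be expressed as median values with respective interquartile range and will be compared by the Mann-Whitney U test". Its only regression model is a stepwise Cox model for the primary outcome and 30-day mortality. The Wilcoxon test it also mentions is for paired comparisons and adjusts nothing between groups.

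The comparators are non-randomised registry patients. Baseline control comes from design: "Propensity matching will be performed among comparators to the 130 patients enrolled in the SAVE trial". The matching criteria are age, Charlson index, co-treatment and admission severity scores, the latter being PSI plus "acute physiology and chronic health evaluation (APACHE) II score, SOFA score and WHO severity classification of COVID-19". SOFA is on that list; the Appendix IV symptom score is not.

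**The concern.** A change score contains the day-1 score with a minus sign, so it carries day-1 noise that a baseline-adjusted comparison removes. The planned test therefore has less power than the same data allow.

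The second issue is bias. Where scores regress to the mean, the group that starts worse tends to improve more without any drug effect. Randomisation would keep the expected day-1 gap at zero; here only matching does so, and the symptom score is not matched. At stake is the reading of four secondary clinical endpoints: a real effect may be missed, or a symptom improvement may be credited to the drug when it reflects a worse start. The binary primary endpoint is not affected.

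**Working it through.** The plan states no power, SD or effect size for these endpoints, so there is no figure of its own to reproduce.

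**Inputs.** From the SAP: 130 trial patients against 130 comparators, and a two-sided 0.05 level. Assumed: scores with SD 1 at both visits, bivariate normal, with day-1/follow-up correlation rho of 0.3, 0.5 or 0.7.

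**Power**
- Variance of a change score: 2(1 - rho).
- Residual variance after adjusting for the day-1 score: 1 - rho².
- Ratio of the two: 2/(1 + rho), which is the factor by which the unadjusted analysis needs more patients.
- Effect giving a t-test on change 80% power: d = (1.96 + 0.842) × sqrt(2(1 - rho)) × sqrt(2/130).
- For Mann-Whitney, the change variance is divided by 0.955, its efficiency relative to the t-test for normal data.

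| rho | Variance, change | Variance, adjusted | Ratio | d (SD) | Power, Mann-Whitney on change | Power, adjusted |
|---|---|---|---|---|---|---|
| 0.3 | 1.40 | 0.91 | 1.54 | 0.411 | 78% | 94% |
| 0.5 | 1.00 | 0.75 | 1.33 | 0.347 | 78% | 90% |
| 0.7 | 0.60 | 0.51 | 1.18 | 0.269 | 78% | 86% |

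Simulation with 3,000 runs per setting agrees: Mann-Whitney 77-79%, adjusted model 93%, 90% and 86%. The loss is about 8 to 15 points. Matching does not remove it: with exact matching on the day-1 score, simulated power was 84/80/79% for Mann-Whitney on change and 94/89/85% with adjustment (rho 0.3/0.5/0.7).

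**Type I error with no drug effect.** Two data models were simulated, because the answer depends on which one holds.

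*Model A, regression to the mean:* the later score depends on group only through the day-1 score. A day-1 gap g then produces a spurious difference in change of -(1 - rho) × g. At g = 0.25 and rho = 0.5 this is -0.125 SD.

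*Model B, stable difference:* the groups differ by the same amount g at both visits. The change score is then unbiased, and the adjusted model is off by (1 - rho) × g.

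| Day-1 gap (SD) | Model A: Mann-Whitney, rho 0.3 / 0.5 / 0.7 | Model A: adjusted | Model B: Mann-Whitney | Model B: adjusted, rho 0.3 / 0.5 / 0.7 |
|---|---|---|---|---|
| 0.1 | 8 / 7 / 6% | about 5% | about 5% | 9 / 8 / 7% |
| 0.25 | 22 / 18 / 11% | about 5% | about 5% | 30 / 21 / 13% |
| 0.5 | 65 / 50 / 34% | about 5% | about 5% | 81 / 62 / 38% |

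The normal approximation for Mann-Whitney under Model A at 0.25 SD gives 21/17/12%, so about 12-22% is a fair range allowing for simulation error.

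**The case against.** The strongest objection concerns bias. A reader might infer that any baseline difference becomes a false drug effect under the planned test, and that adjustment cures it. The documents do not support that. It holds under Model A only. Under Model B, which is plausible for non-randomised groups, the planned test keeps its 5% level and the adjusted model does not. Nothing in the protocol or SAP says which model applies. This stands: the bias claim must be conditional, and adjustment cannot simply replace the change-score analysis.

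A reader might also apply the 12-22% to SOFA. SOFA is matched, together with APACHE II, PSI and WHO class. Matching is on the admission value while change runs from the start of treatment, but the documents state no interval between the two, so a material gap is conjecture. At an assumed residual gap of 0.1 SD, type I error is 6-8%. This stands too.

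It can further be said that the between-group test is inferred. Only the first secondary endpoint mentions comparators, and nothing shows that registry patients have Appendix IV scores on days 1, 7 and 14. The first part is weak: Mann-Whitney is a two-group test, and the SAP assigns it to quantitative secondary outcomes. The second part stands. Without comparator day-1 and follow-up scores, however, the planned change comparison could not be made either.

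Finally, these are secondary endpoints with no stated power, and a rank test on change is a recognised choice for bounded ordinal scores. That limits the weight of the point; it does not answer the power loss.

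**Conclusion.** The point holds in a limited form. No passage adjusts the four change comparisons for the day-1 score. Under assumed correlations of 0.3 to 0.7 and normal scores, this means about 78% power where 94% to 86% was available, or 1.54 to 1.18 times the patients for the same precision. This applies to the symptom score and SOFA alike.

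For the symptom score there is a further, conditional risk: it is not matched, and with regression to the mean and an assumed 0.25 SD day-1 gap the planned test would reject in about 12-22% of trials of an inactive drug. For SOFA the case is mainly one of power. The correlation, SDs and gaps are assumptions, since the documents give none. The plan should be changed, but the primary conclusion does not depend on it.

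**What to change.** For the four endpoints, and wherever comparators have day-1 and follow-up scores:

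- Make the main analysis a model of the day-7 (or day-14) score on group and day-1 score, preferably with the matching variables. Use proportional odds, or ANCOVA with robust standard errors, and report the adjusted odds ratio or difference with a 95% CI.
- Report day-1 balance of both scores after matching.
- Keep Mann-Whitney on the change as a sensitivity analysis, and median change with interquartile range as description.

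The cost is SAP wording. The adjusted analysis needs no data beyond what the change itself requires. The downside is a model assumption (proportional odds or linearity) and possible bias if the groups differ by a stable amount. Showing both analyses next to the balance table would expose such a conflict.

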- Recording of co-administered drugs, absolute blood cell count and differential (if available) and biochemistry (if available)
- Recording of the presence or not of SRF (Appendix V)
- Recording of adverse events (AE) and severe adverse events (SAE)
- Administration of the study drug
- The visit may take place by phone call or through the internet in case of hospital discharge

*Day 6*

This visit will take place on the morning of the sixth day from the start of treatment with the study drug. The following procedures will be done on that day:

- Recording of co-administered drugs, absolute blood cell count and differential (if available) and biochemistry (if available)
- Recording of the presence or not of SRF (Appendix V)
- Recording of adverse events (AE) and severe adverse events (SAE)
- Administration of the study drug
- The visit may take place by phone call or through the internet in case of hospital discharge

*Day 7*

This visit will take place on the morning of the seventh day from the start of treatment with the study drug. The following procedures will be done on that day:

- Recording of co-administered drugs, SOFA score (Appendix III), absolute blood cell count and differential (if available) and biochemistry (if available)
- Scoring of the respiratory symptoms (Appendix IV).
- Recording of the presence or not of SRF (Appendix V)
- Recording of adverse events (AE) and severe adverse events (SAE)
- Sampling of 15 ml of venous blood. Blood analysis will be done as described at the section Laboratory Procedures.
- Administration of the study drug
- The visit may take place by phone call or through the internet in case of hospital discharge. In that case, no blood sampling will take place.

*Day 8*

This visit will take place on the morning of the eighth day from the start of treatment with the study drug. The following procedures will be done on that day:

- Recording of co-administered drugs, absolute blood cell count and differential (if available) and biochemistry (if available)
- Recording of the presence or not of SRF (Appendix V)
- Recording of adverse events (AE) and severe adverse events (SAE)
- Administration of the study drug
- The visit may take place by phone call or through the internet in case of hospital discharge

*Day 9*

This visit will take place on the morning of the nineth day from the start of treatment with the study drug. The following procedures will be done on that day:

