- Recording of co-administered drugs, absolute blood cell count and differential (if available) and biochemistry (if available)
- Recording of the presence or not of SRF (Appendix V)
- Recording of adverse events (AE) and severe adverse events (SAE)
- Administration of the study drug
- The visit may take place by phone call or through the internet in case of hospital discharge

*Day 10*

This visit will take place on the morning of the tenth day from the start of treatment with the study drug. The following procedures will be done on that day:

- Recording of co-administered drugs, absolute blood cell count and differential (if available) and biochemistry (if available)
- Recording of the presence or not of SRF (Appendix V)
- Recording of adverse events (AE) and severe adverse events (SAE)
- Administration of the study drug
- The visit may take place by phone call or through the internet in case of hospital discharge

*Day 14*

This visit will take place on the morning of the 14^th^ day from the start of treatment with the study drug. The following procedures will be done on that day:

- Recording of co-administered drugs, SOFA score (Appendix III), absolute blood cell count and differential (if available) and biochemistry (if available)
- Scoring of the respiratory symptoms (Appendix IV).
- Recording of the presence or not of SRF (Appendix V)
- Recording of adverse events (AE) and severe adverse events (SAE)
- The visit may take place by phone call or through the internet in case of hospital discharge

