# STUDY ENDPOINTS

## Primary study endpoint

The primary study endpoint is the rate of patients who will develop SRF (see Appendix V for definition) until day 14. Patients dying before study visit of day 14 are considered achieving the primary endpoint.

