# APPENDIX III The SOFA score

| **Variable** | **0 points** | **1 point** | **2 points** | **3 points** | **4 points** |
| --- | --- | --- | --- | --- | --- |
| PaO_2_/FiO_2_(mmHg) | ≥400 | <400 | <300 | <200 | <100 |
| Platelets (per mm^3^) | ≥150 | <150 | <100 | <50 | <20 |
| Hypotension | MAP≥ 70 mmHg | MAP<70 mmHg | Dobutamine whatever dose | Adrenaline≤0.1* or  Noradrenaline  ≤0.1* | Adrenaline>0.1* or  Noradrenaline >0.1* |
| Glasgow Coma Scale | 15 | 13-14 | 10-12 | 6-9 | <6 |
| Bilirubin (mg/dl) | <1.2 | 1.2-1.9 | 2.0-5.9 | 6.0-11.9 | ≥12 |
| Creatinine (mg/dl) or Urine output | <1.2 | 1.2-1.9 | 2.0-3.4 | 35-4.9 or <500ml/day | ≥5.0 or  <200ml/day |

*μg/kg/min

Each variable is scored between 0 and 4. The SOFA score is the sum of the score of each variable

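### The SAP gives deaths and post-discharge missing SOFA no place in the Mann-Whitney comparisons of SOFA and respiratory score change; leaving them out dilutes a true benefit and, under stronger assumptions, can reverse it

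*Supplement*

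**What the plan says.** The final protocol's list of secondary endpoints includes "Change of SOFA score between days 1 and 14" and "Change of scoring for respiratory symptoms between days 1 and 14", and both also appear for days 1 to 7. These are four of ten secondary endpoints. The SAP's rule for outcomes of this kind is a between-group test: "Quantitative secondary outcomes will be expressed as median values with respective interquartile range and will be compared by the Mann-Whitney U test".

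Death is given a value in the primary endpoint: "Patients dying before study visit of day 14 are considered achieving the primary endpoint". No such rule exists for the scores.

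The visit schedule creates gaps. At days 7 and 14, "The visit may take place by phone call or through the internet in case of hospital discharge". For a remote day 7 visit the protocol adds: "In that case, no blood sampling will take place". The day 14 entry reads "Recording of co-administered drugs, SOFA score (Appendix III), absolute blood cell count and differential (if available) and biochemistry (if available"), so blood counts and biochemistry are recorded only when they happen to exist.

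Appendix III builds SOFA from six items, among them PaO2/FiO2, platelets, bilirubin and creatinine, and "The SOFA score is the sum of the score of each variable". Appendix IV scores cough, chest pain, dyspnoea and sputum by description. The SAP names the intention-to-treat population but has no missing-data rule.

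**The concern.** A Mann-Whitney test needs a value, or at least a rank, for each patient. Without a rule, a patient who died before day 7 or day 14 drops out, although this is the worst outcome. A patient discharged and seen by phone drops out of the SOFA comparison, although this is usually among the best outcomes. Both events happen after baseline, and treatment may influence both. Propensity matching balances baseline characteristics and does not protect against this selection.

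If anakinra prevents deaths or speeds discharge, the SAVE patients who still have a SOFA are, relative to the comparators, weighted towards the sicker survivors. A true benefit is then diluted and may be reversed. The choice of handling is also left open until after the data are seen, in an open-label trial with non-randomised comparators.

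**Working it through.** The documents give no figure for these comparisons, so there is none to reproduce. They also give no death rate, discharge rate or SD for SOFA change. All such inputs below are assumptions, and ranges are shown.

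**1. Which patients lose a score**

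| Patient | SOFA change | Respiratory score change |
|---|---|---|
| Died before the visit | none | none |
| Discharged, remote visit | not obtainable in full | obtainable by phone |
| In hospital | obtainable if laboratory values exist | obtainable |

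**2. Size of the shift in the estimate (SOFA, day 14)**

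The test targets θ = P(SAVE better) + ½P(tie); θ > 0.5 favours SAVE.

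Model: comparators' change ~ N(0, σ²), SAVE ~ N(−0.3, σ²), lower being better. In each group the sickest fraction dies and the healthiest is discharged without a SOFA. The observed-only test uses the rest. With deaths 10% v 20% and discharge 60% v 45% (SAVE v comparators), that is 1 − 0.10 − 0.60 = 30% of SAVE and 1 − 0.20 − 0.45 = 35% of comparators. The benchmark ranks deaths worst and discharges best. The simulation used 400,000 per group; variants of the set-up move results by about 0.01.

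| Deaths; discharge (SAVE v comparators) | SD (points) | θ observed-only | θ all ranked |
|---|---|---|---|
| 10% v 20%; 60% v 45% | 1 | 0.43 | 0.58 |
| same | 1.5 | 0.34 | 0.57 |
| same | 3 | 0.26 | 0.56 |
| 8% v 15%; 60% v 50% | 1 | 0.53 | 0.56 |
| same | 1.5 | 0.44 | 0.55 |

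**3. Relaxing the model (SD 1.5, first set of rates)**

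- *Severity predicts death and discharge imperfectly.* Observed-only θ is 0.46 at correlation 0.8, 0.49 at 0.6 and 0.50 to 0.51 at 0.5.
- *Both groups share the same severity thresholds.* The shift is 0.3/1.5 = 0.2 SD. Comparator deaths of 20% put the threshold at z = 0.842, so SAVE deaths are 1 − Φ(0.842 + 0.2) ≈ 15%. Comparator discharge of 45% puts it at z = −0.126, so SAVE discharge is Φ(−0.126 + 0.2) ≈ 53%. Observed-only θ is 0.51 to 0.52 against 0.55 all ranked: diluted, not reversed.

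**4. What happens to the test at 130 per group**

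A separate simulation used rounded scores with SD 2, two-sided 5% tests and 2,000 runs per case. Here the complete-data test ranks deaths worst and has every survivor's score.

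| Case (comparators v SAVE) | θ observed-only | θ complete | Result |
|---|---|---|---|
| 0.25 SD benefit, common thresholds, deaths 20% v 14%, no remote visits | 0.553 | 0.568 | power 28% instead of 48% |
| Same, remote visits 30% v 39% | 0.525 | 0.568 | power 7% instead of 48% |
| 0.25 SD benefit, deaths 10% v 10%, remote 30% v 45% | 0.517 | 0.565 | diluted |
| Drug only halves deaths (20% v 10%), rescued patients keep bad scores, no remote visits | 0.445 | 0.510 | significant in the wrong direction in 29% of runs |
| 0.25 SD benefit, deaths 20% v 10%, remote 30% v 45% | 0.435 | 0.572 | wrong direction in 26%; complete test favours SAVE in 54% |

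The first and fourth rows need no remote visits. Their mechanism, death alone, therefore applies to the respiratory score as well.

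**The case against.** The strongest reply is that these are secondary endpoints and a mortality effect would not be hidden. Deaths count in the primary endpoint, in 30- and 90-day mortality, and in the survival and Cox analyses. That stands. It limits the consequence but does not tell the analyst what to do with the four score comparisons.

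A reader might infer more than the documents support:

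- *That the plan would show anakinra as worse.* Reversal needs strong assumptions: severity almost wholly deciding death and discharge, rescued patients who stay very ill, or clearly more frequent discharge on anakinra. Under common thresholds the benefit shrinks and power falls, but the direction holds.
- *That the SAP prescribes an observed-values analysis.* It does not say so. This follows from its silence, because a rank test omits a patient without a value.
- *That all four endpoints rest on inpatients only.* Symptoms can be scored by phone. For SOFA, the protocol permits remote visits without requiring them, and the availability caveat is attached to the blood count and biochemistry, not to the SOFA entry.
- *That only 30% to 35% of patients would contribute.* That figure is the assumed rates subtracted from 100%. It is not a property of the plan and does not carry over to day 7.

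Giving discharge the best rank is also open to objection. The comparison is open-label, the comparators come from registry departments, and SAVE patients may continue injections at home. Earlier discharge could reflect logistics that the rule would credit to anakinra. This stands, and it is why that rule belongs in a sensitivity analysis.

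**Conclusion.** The gap is real and can be read from the documents alone. Four secondary endpoints have a named test but no place for deaths, and two of them also have none for a SOFA unobtainable at a remote visit. Across the cases examined, leaving these patients out moved the estimate towards no effect or against anakinra. The robust consequence is dilution: with a 0.25 SD benefit and common thresholds, power falls from 48% to 28% through deaths alone and to 7% with remote visits added. Reversal is possible but conditional; the observed-only values of 0.43 to 0.26 assume that severity fully determines death and discharge.

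The documents also do not say whether comparators had scores taken at days 7 and 14. If their SOFA were complete among survivors and 30% of SAVE patients lacked it (deaths 20% v 10%), the wrong direction would be significant in 91% of runs. The point should be corrected, with weight suited to secondary endpoints.

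**What to change.** Keep the Mann-Whitney test and add a short rule to the SAP:

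- Rank death before the visit as the worst outcome for all four endpoints, in both groups, in line with the primary endpoint's treatment of death.
- For SOFA missing after discharge alive, pre-specify one rule, applied identically to SAVE patients and comparators. Show best rank for discharge as a sensitivity analysis, because discharge practice may differ between SAVE sites and registry departments. Ranking deaths does not by itself solve this part.
- Report the number with an observed score per group at each visit, and give observed-only medians and interquartile ranges as descriptive.

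This takes a few sentences and no new data. The cost is in interpretation: the result becomes a rank comparison of death and score, no longer a pure change in score.
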